## Methods/Design

### Aims

The primary aim of InterHerz is to investigate whether the proven web-based treatment Deprexis is effective to reduce depression and perceived stress in cardiac patients. Secondary aims are to examine the mid-term effects of Deprexis on depression, perception of stress, social support, and changes in health behavior after six months follow-up.

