### Inclusion and exclusion criteria

Adults who suffer from any cardiovascular disorder (including coronary heart disease, chronic heart failure, and arrhythmias) can apply to participate. Patients are included if they return the informed consent, are 18 years or older, have symptoms of depression (as defined by scoring above a cut-off of 9 on the Beck Depression Inventory (BDI-II)), are of sufficient knowledge of German language, and have access to the Internet. If patients have any acute health threatening disease (for example, cancer), a severe psychiatric illness (for example, psychosis, dementia), suicidal thoughts or plans, or an unstable heart condition, they are excluded from the study. Participants will remain in the study in case of further progression of heart disease during study participation.

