### Assessment

The efficacy of the intervention is assessed post-treatment (T2) and additionally at 6 months follow-up (T3). Pre-treatment assessment (T0) is conducted by a psychologist before the randomization procedure to assess the level of depression, and to collect information on perceived stress, perceived social support and quality of life. At baseline, we further assess medical information on the disease, duration of the disease, time of the event, risk behavior (for example, smoking, low physical activity, poor diet), and medication or other psychotherapeutic treatments. Moreover, a clinical diagnostic interview is conducted by phone. To address the research question, depression levels are measured during treatment (T1), and treatment satisfaction is measured at the end of the treatment (T2).

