### Measures

The German version of the Beck Depression Inventory (BDI-II) [40] is administered to assess the level of depressive symptoms. Ten points or more is to be considered a clinically relevant score for depressive symptomatology. All patients with depressive symptoms above this cut off are asked to fill out the German version of the Patient Health Questionnaire (PHQ-D) [41] and are additionally interviewed by a psychologist with the Structured Clinical Interview for DSM diagnosis (SCID) to classify patients as clinically depressed according to the American Psychiatric Association Diagnostic and Statistical Manual [42]. Stress perception is assessed by the Perceived Stress Questionnaire PSQ [43] and perceived social support by the German version of the self-rated 7-item ENRICHD Social Support Inventory (ESSI) [44]. The World Health Organization (WHO) quality of life-BREF (WHOQOL-BREF) (German version) [45], a brief form of a transcultural quality of life assessment instrument developed by the WHO, is used to measure quality of life. Client satisfaction is assessed post-treatment with the German version of the Client Satisfaction Questionnaire (CSQ) [46]. Medication and compliance with medication are assessed by free text and health-related lifestyle (for example smoking, physical activity, diet) with dichotomous items in line with earlier studies by the research team [47].

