### Statistical analyses

We will analyse the longitudinal data according to a completer analysis (after the intervention) and in addition we will use intent-to-treat analysis including patients who drop out during the intervention or waiting period. The efficacy of the intervention will be estimated using analysis of variance with baseline values as covariates and additional assessments conducted after 5 sessions (midterm) and after 10 sessions (post). The primary endpoint will be depressive symptoms measured by BDI II and a diagnostic interview after 10 weeks. Secondary end points will be perception of stress, social support, quality of life and compliance. Long-term stability of the efficacy of the intervention will be analysed by comparisons of pre-treatment and follow-up assessments of depression in all participants (InterHerz and waitlist control group) using the *t*-test of dependent samples, and pre-treatment to follow-up effect sizes will be calculated. For the prediction of treatment success we will use clinical variables (for example, severity of cardiac disease), sociodemographic variables (for example, age, gender) and process measures (for example, working alliance). Since missing values are a critical issue in longitudinal studies we will use a statistical algorithm for the estimation of missing values as implemented in SPSS.

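### The primary endpoint is two measures of different kinds (BDI-II score and diagnostic interview) with no success rule, and the primary aim includes perceived stress, which the analysis section ranks as secondary

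*Protocol article*

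**What the plan says.** All references are to the protocol article.

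- **Statistical analyses**, primary endpoint: "The primary endpoint will be depressive symptoms measured by BDI II and a diagnostic interview after 10 weeks".
- **Measures**: the BDI-II assesses the level of depressive symptoms. The structured interview is used "to classify patients as clinically depressed according to the American Psychiatric Association Diagnostic and Statistical Manual". No symptom score from the interview is described.
- **Statistical analyses**, model: "The efficacy of the intervention will be estimated using analysis of variance with baseline values as covariates".
- **Aims**: the primary aim is to find out whether "the proven web-based treatment Deprexis is effective to reduce depression and perceived stress in cardiac patients". The six-month effects, including those on stress, are listed separately as secondary aims.
- **Statistical analyses**, secondary endpoints: "Secondary end points will be perception of stress, social support, quality of life and compliance".
- **Sample size calculation**: 80 patients (40 per arm), two-sided 0.05, 80% power, a medium between-group effect and correlations between pre- and post-assessment. No outcome is named, and neither the effect nor the correlation has a number.

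**The concern.** A primary endpoint has to fix what counts as success before the data are seen. Here one label covers a continuous score and a diagnostic classification, and they can disagree: mean scores may fall while the proportion diagnosed hardly moves, or the reverse. Three readings are open: either measure may succeed, both must succeed, or the two are combined. The article chooses none of them.

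The first two readings have opposite costs. If either measure may succeed at 0.05, the error rate exceeds the stated level. If both must succeed, the stated power no longer describes the chance of a positive trial. While the rule is unstated, it could be settled after the results are known.

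Perceived stress is a separate conflict of rank. Because the Aims section lists the six-month effect on stress as secondary, the stress in the primary aim must be the short-term effect. That same outcome is then called secondary in the analysis section, and both statements cannot stand.

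**Working it through.** **1. The plan's own figure.** The article gives alpha 0.05 two-sided, power 80% and 40 per arm. It does not give the effect size or the pre-post correlation r. I assume that medium means d = 0.5 and vary r. With baseline adjustment:

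n per arm = 2 (z₀.₉₇₅ + z₀.₈₀)² (1 − r²) / d², where z₀.₉₇₅ + z₀.₈₀ = 1.960 + 0.842 = 2.802.

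| r | n per arm | Total | Power at 40 per arm |
|---|---|---|---|
| 0 | 63 | 126 | 61% |
| 0.5 | 48 | 96 | 73% |
| 0.6 | 41 | 82 | 80% |
| 0.7 | 33 | 66 | 88% |

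For r = 0.6: 2 × 7.849 × 0.64 / 0.25 = 40.2, rounded up to 41. So 80 is plausible for one continuous outcome with r near 0.60. It cannot be confirmed without the missing inputs, and it is not shown to be wrong.

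**2. Either measure may succeed, each at 0.05.** With independent tests, the chance of at least one false positive is 1 − 0.95² = 0.0975. Values for correlated tests come from simulating bivariate normal test statistics (1,000,000 draws).

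**3. Both must succeed, each with 80% power.** With independent tests, joint power is 0.80 × 0.80 = 0.640. For correlated tests, the same simulation is shifted by 2.802.

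| Correlation of the two tests | Type I error (either) | Joint power (both) |
|---|---|---|
| 0 | 0.0975 | 0.640 |
| 0.3 | 0.0950 | 0.666 |
| 0.5 | 0.0905 | 0.687 |
| 0.7 | 0.0834 | 0.713 |
| 0.9 | 0.0703 | 0.750 |

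Two measures of one construct should correlate, so the zero row is an outer bound. Even at 0.9 neither stated figure is met.

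**4. Either may succeed, with the error held at 5% by Bonferroni (0.025 each).** With d = 0.5 and the r that gives 80% power at 40 per arm (about 0.60), power for one measure is Φ(2.802 − 2.241) = Φ(0.560) = 0.712. Restoring 80% for that measure takes 2 × (2.241 + 0.842)² × 0.64 / 0.25 = 48.7, so 49 per arm or 98 in total.

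**5. Is 80% power realistic for the diagnosis?** The article gives no diagnosis rates, so these are assumptions. At 40 per arm, the power of a two-proportion test on the diagnosis alone is:

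- 50% versus 25% still diagnosed: 64%
- 50% versus 30% still diagnosed: 45%
- a shift equivalent to d = 0.5, with control rates from 50% to 90%: about 29% to 51%

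These are not joint powers. Each is a ceiling on joint power. If the diagnosis test were independent of a BDI-II test with 80% power, the first two would give 0.80 × 0.641 = 0.51 and 0.80 × 0.445 = 0.36.

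**The case against.** The strongest defence is that the endpoint is written in the singular: one construct, depressive symptoms, seen through two instruments. The Discussion presents the interview as adding depth to self-report. The article is also a condensed account, and multiplicity rules and the model for a binary outcome commonly sit in an analysis plan that is not shown. Part of this stands. The absence of a model for the diagnosis is not held against the article, and the shared construct makes the lower end of the error range more credible. But the choice of primary endpoint is made here, and the wording does not identify one.

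A reader might infer more than the document supports:

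- **That no interview is planned at 10 weeks**, because the Assessment section mentions it only among the baseline procedures ("Moreover, a clinical diagnostic interview is conducted by phone"). The Abstract's Methods/Design paragraph says that pre-, post- and follow-up assessments use diagnostic interviews.
- **That there are three primary endpoints**, which would put the error at 10.9% to 14.3%. Perceived stress is never declared a primary endpoint. The defect there is a conflict between aim and endpoint list.
- **That patients without a diagnosis at entry make the endpoint unworkable**, since eligibility rests on symptoms "as defined by scoring above a cut-off of 9 on the Beck Depression Inventory (BDI-II") rather than on a diagnosis. The article does not define the endpoint as remission, and presence of a diagnosis at 10 weeks can be assessed in every patient.
- **That 80 patients is the wrong number.** The check above finds it plausible for one continuous outcome.

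**Conclusion.** The point holds in this form. The article names two measures of different kinds as its primary endpoint without a success rule, and its primary aim and endpoint list disagree on perceived stress.

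If either measure may succeed at 0.05, the type I error is about 8.3% to 9.8% (correlation 0.7 to 0) against the stated 5%. If both must succeed, joint power is about 64% to 69% (correlation 0 to 0.5) against the stated 80%. The second range assumes 80% power for each measure and falls if the diagnosis test has less, which depends on rates that the article does not give. The Bonferroni figures rest further on d = 0.5 and r near 0.60.

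That the sample size was built on the BDI-II is an inference. The pre-post correlations point to a continuous score, but the section names no outcome. The main conclusion does not depend on that inference.

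**What to change.** 1. In Statistical analyses, name the BDI-II total score at 10 weeks as the sole primary endpoint.
2. Make interview diagnosis at 10 weeks a secondary endpoint, with an analysis suited to a binary outcome, for example logistic regression adjusted for baseline diagnosis.
3. In Aims, limit the primary aim to depression and move perceived stress at 10 weeks to the secondary aims, so that it agrees with the endpoint list.
4. In Sample size calculation, state that the calculation refers to the BDI-II, if that is so.

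This changes wording only. No patients or assessments are added, and the planned 80 patients stand. The downside is small: diagnosis and perceived stress lose primary status. The article reports recruitment as ongoing, so the change should be made and dated before any outcome data are examined.

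If the sponsor wants both depression measures to stay primary, the article must say whether either or both must succeed, and the sample size must be recalculated for that rule.

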## Discussion

This study examines the efficacy of a web-based, guided self-help treatment for depressed cardiac patients in terms of depressive symptoms, perception of stress, social support, quality of life and health behavior change. So far, no randomized controlled trial exists that specifically evaluates the efficacy of a web-based psychological treatment for cardiac patients with depressive symptoms. Given the fact that cardiac patients have limited access to psychological treatments, it is important to know whether such an easily accessible and low-cost intervention has future potential to be an integrative part in the rehabilitation of cardiac patients and in the general health system.

As patients with heart disease will be on average a relatively old patient group, we asked patients in a cardiac rehabilitation unit about the use of the Internet for health-related information as part of our preparation of the study protocol. In a sample of 59 patients (mean age 67 yrs, SD 8.6) 71% of the cardiac patients reported that they had their own access to the Internet and would use it as a source for health-relevant information on a regular basis. Furthermore, over 80% expressed interest in using a new web-based intervention. Whether these patients would benefit from a web-based psychological treatment specifically developed for depression remains unclear.

There are limitations to the study design. First, the intervention is not specifically adapted for cardiac patients and the effect on cardiac health will not be in the main focus of the investigation. Second, participants of the waitlist receive access to the psychological treatment after a delay of ten weeks, therefore, we will not be able to compare groups at the 6-month follow-up.

The study has several strengths. It has a high external validity since patients are recruited from cardiology institutions and organizations, and since patients suffering from various cardiovascular disorders are included. Depression is assessed by self-rated instruments and a diagnostic interview. This allows more profound knowledge of the actual mental state of the participant. Furthermore, to our knowledge this is the first web-based psychological treatment for cardiac patients using a proven web-based depression tool. This investigation will allow us to extend our knowledge of the benefits and limits of a web-based psychological treatment that integrates the most recent treatment approaches for depressed cardiac patients.

## Trial status

Recruitment of participants is ongoing; it began in March 2012 and is expected to end in June 2013.

## Abbreviations

BDI II: Beck Depression Inventory; CBT: Cognitive behavioral therapy; CREATE: Canadian cardiac randomized evaluation of antidepressant and psychotherapy efficacy; CSQ: Client Satisfaction Questionnaire; ENRICHD: Enhancing recovery in coronary heart disease patients with depression; ES: Effect size; ESSI: ENRICHD Social Support Inventory; IPT: Interpersonal psychotherapy; PHQ: Patient Health Questionnaire; PSQ: Perceived Stress Questionnaire; SCID: Structured Clinical Interview for DSM disorders; WHO: World Health Organisation; WHOQOL-BREF: WHO quality of life-BREF.
